**Intervention**

**Ingredients of TSF**： TSF consists of radix astragali (Huangqi) 30 grams, rehmannia dride rhizome (Shengdi) 12 grams, prepared rhubarb (Zhidahuang) 6 grams, notoginseng (Sanqi) 3 grams, evonymus alata (Weimao)15 grams, medicinal cornel (Shanzhuyu) 9 grams and fructus aurantii (Zhiqiao) 10 grams in dried raw material. TSF is manufactured by Jiangyin Tianjiang Pharmaceutical Company Limited (Lot No. 0606320), and restored at 15℃ -30℃.

**Ingredients of placebo:** lactose, dextrin and artificial food coloring. Placebo is also manufactured by Jiangyin Tianjiang Pharmaceutical Company Limited.

**Allocation of drugs:** Drugs with specific codes will be assigned to each hospital, due to the allocation design for each unit. Each study unit designates an experimental drug administrator. The researchers will screen qualified subjects. After subjects sign informed consent and complete the run-in period, the drug administrator will allocate drugs according to the code order and record the allocating information in the "clinical trial drug use record" form. The researchers will in charge of recording how many packages of drugs are allocated by the drug administrator, taken by the participant and returned to the uint, at each visit of a participant. The unused drugs will be returned to sponsor and destroyed according to certain procedure.

**Basic treatments:** All participants will be instructed to keep a low-salt diabetic diet, including a reasonable match of calories, protein, carbohydrates and fat, and keep a fixed level of exercise based on their age, urine protein level and cardiac function. According to ADA’s guideline, all participants will receive either an ACEI or ARB agent treatment. Antihypertensive treatment, glycemic control and antilipemic agents were adopted as conventional treatments. All the western drugs will be given open-labelled.

**Treatment for TSF group:** In addition to the basic treatments, each participant in the intervention group will be prescribed TSF. TSF will be administered to participants with two packages (8 grams) per time and twice a day.

**Treatment for placebo group:** In addition to the basic treatments, each participant in the placebo group will receive placebo medicine with the same appearance, shape and smell as TSF. Furthermore, the method and time of taking drugs will be the same as that in the treatment group.

**Duration of intervention:** All participants have to visit researchers every 4 weeks with a total of 24 weeks. Table 1 is an overview of specific measurements in each visit time.

Table 1: The content of data capture

| Item | Screening period (unit:weeks) | Intervention period (unit:weeks) | | | | | | |
| --- | --- | --- | --- | --- | --- | --- | --- | --- |
|  | -2 | 0 | 4 | 8 | 12 | 16 | 20 | 24 |
| Record of medical history | √ |  |  |  |  |  |  |  |
| General physical examination | √ | √ | √ | √ | √ | √ | √ | √ |
| Blood and urine regulation | √ | √ |  |  | √ |  |  | √ |
| Electrocardiogram | √ | √ |  |  | √ |  |  | √ |
| ALT, AST | √ | √ |  |  | √ |  |  | √ |
| BUN, Cr, eGFR | √ | √ |  |  | √ |  |  | √ |
| HbA1c | √ | √ |  |  | √ |  |  | √ |
| UAER &24h urinary protein | √ | √ |  |  | √ |  |  | √ |
| serum TC, TG, LDL, VLDL | √ | √ |  |  | √ |  |  | √ |
| WHO QOL-BREF, DQOL |  | √ |  |  | √ |  |  | √ |
| Evaluation of TCM Syndrome | √ | √ | √ | √ | √ | √ | √ | √ |
| Drug Distribution and record |  | √ | √ | √ | √ | √ | √ |  |
| Left drugs Retrieval |  |  | √ | √ | √ | √ | √ | √ |
| Adverse events |  | √ | √ | √ | √ | √ | √ | √ |

√：Item need to be done during different period

**Outcome measurements**

**Primary outcomes**

UAER for DKD patients in the microalbuminuria stage and 24-hour urinary protein excretion amount for DKD patients in the macroalbuminuria stage are considered as the primary outcome measurements.

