**Sample size**

The sample size has been calculated according to our preliminary results [[[8]](#endnote-9)]. The mean reduction of UAER in the control group was 30.19, and that in TSF group was 81.67. The ratio of patients between the treatment group and the placebo group is designed as 2:1. The sample size has been estimated to be 56 in the control group, and 112 in the treatment group. Assuming a dropout rate of 15%, 90% power to detect and a 0.05 two-side level of significance, the sample size of DKD patients has been estimated to be 192.

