**Blindness**

Double-blinding method is adopted in this study. As the package, color, smell and taste of the placebo is the same as TSF, so researchers and participants won’t know the kind of medicine and group allocation. It was not allowed for the drug administrator to neither contact with investigators, nor exchange information with patients. They are trained how to illustrate the usage and dose of this formula for the patients but not to convey any treatment information to participants.

The outcome assessment will be conducted by independent researchers who don’t know the group allocation of patients.

Figure 1: The flowchart of the trial:

Screening for type 2 diabetic kidney disease with microalbuminuia /marcoalbuminuia individuals

Sign consent

Inclusion criteria achieved?

Run-in period (2 weeks)

NO

Excluded

Primary outcome:

UAER & 24h urinary protein

Secondary outcome (1):

Scr，BUN， eGFR

Blood lipid

Secondary outcome (2):

TCM syndrome & quality of life

Completed the 24-wk administration

**TSF group**：

TSF+ACEI/ARB

**Placebo group**： Placebo + ACEI/ARB

Visits and clinical measurements, medication

at 4,8,12,16,20,24 weeks

YES

Randomization

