**Patient ratio**

**2 : 1**

**Participants**

**Diagnosis criteria**

Patients with type 2 diabetes are diagnosed according to the American Diabetes Association criteria [[[9]](#endnote-10)],and micro-albuminuria and macro-albuminuria stages of DKD are defined in the light of the K-DOQI guidelines [[[10]](#endnote-11)], and the Chinese syndrome differentiation type as Qi and Yin deficiency with blood stasis is based on the guiding principle of clinical research on new drugs of traditional Chinese medicine [[[11]](#endnote-12)].

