**Inclusion and exclusion criteria**

Patients aged 25-75 years who have been diagnosed as type 2 diabetes and DKD will be included in the study and meet the following inclusion criteria: the Chinese syndrome differentiation type as Qi and Yin deficiency with blood stasis; blood pressure < 140/90mmHg; fasting blood glucose (FBG) ≤ 7.8 mmol/L and glycosylated hemoglobin (HbA1C) ≤7.5%; UAER>20 μg/min , and/or 24-hour urinary protein level 0.5~2.0 g, and estimated glomerular filtration rate (eGFR) estimated by Cockcroft-Grault equation ranging from 60ml/min to130ml/min; signed written informed consent.

Patients will be excluded if they had a history of primary kidney diseases or systematic disease with elevated urinary protein. Other major exclusion criteria were other endocrine or metabolic disease; mental disorders; women in pregnancy or lactation; herb allergy; a history of myocardial infarction, angina pectoris or other recent cardiovascular problems (including cerebrovascular events) within the last 3 months or recent infection within the last 4 weeks; fasting serum triglyceride > 10 mmol/L; impaired hepatic function, defined as Alanine transaminase (ALT) and/or Aspartate aminotransferase (AST) level≥2 times the upper limit of the nomal reference range. Patients who take glucocorticosteroid, thiazide diuretics and niacin within the last 3 months will also be excluded.

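### Primary outcomes are split by DKD stage, but the single 0.05 level and 90% power are set for UAER over all patients, and no rule for success is fixed

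*Protocol*

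**What the plan says.** The Protocol's Primary outcomes section assigns one measure to each stage: "UAER for DKD patients in the microalbuminuria stage and 24-hour urinary protein excretion amount for DKD patients in the macroalbuminuria stage". Both carry primary status, with no ranking between them. Under Diagnosis criteria, "micro-albuminuria and macro-albuminuria stages of DKD are defined in the light of the K-DOQI guidelines", so the two stages are treated as separate categories.

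The Sample size section uses UAER only: "The mean reduction of UAER in the control group was 30.19, and that in TSF group was 81.67". It arrives at 56 controls and 112 patients on TSF, then 192 in total, under a single set of error rates: "Assuming a dropout rate of 15%, 90% power to detect and a 0.05 two-side level of significance". Neither the 168 evaluable patients nor the 192 are divided by stage. No planning figure is given for 24-hour urinary protein.

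Figure 1 (under Blindness) gives the primary outcome as "UAER & 24h urinary protein", with no mention of stage. Table 1 has both measures taken in all patients at weeks -2, 0, 12 and 24.

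**The concern.** The trial that was sized differs from the trial whose primary outcomes are defined. The sizing is one comparison of UAER in everyone. The definition is two comparisons, each in part of the patients, and only one of them uses UAER.

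The protocol also does not fix whether efficacy needs either result, both, or a combined result. That choice decides the trial's false-positive rate and its power. Because both measures are collected in everyone and Figure 1 omits the stage restriction, more than one version of the primary analysis could be run on the same data. If the choice is still open once results are known, neither "a 0.05 two-side level of significance" nor the stated 90% power describes the trial's main claim.

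**Working it through.** **Inputs from the Protocol (Sample size).** Difference in mean UAER reduction: 81.67 - 30.19 = 51.48 (unit not given). Evaluable patients: 56 and 112, ratio 1:2. Two-sided alpha 0.05, power 0.90.

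**The plan's own figure.** No SD is stated, so 56/112 cannot be reproduced independently. It can be solved backwards. With n controls and 2n on TSF, n = 1.5 × (1.960 + 1.282)² / d².
- Setting n = 56 gives d = √(1.5 × 10.507 / 56) = 0.53, and SD = 51.48 / 0.5305 = 97.
- Forwards, an SD of 95, 97 or 100 gives 54, 56 or 60 controls.
- The stated size therefore fits one UAER test in all 168 patients at 0.05, if the SD is about 97.

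**Error rate under each possible rule.** The first two lines assume that the stages share no patients, so the tests are independent.
- Either result suffices, 0.05 each: 1 - 0.95² = 0.0975. For a false claim of benefit only: 1 - 0.975² = 0.0494, against 0.025.
- Either suffices, 0.025 each: 1 - 0.975² = 0.0494.
- Both required: 0.05² = 0.0025 if neither effect exists, and never above 0.05.
- One combined or stratified test: 0.05.

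**Power when stages are tested separately.** The stage shares are not in the protocol, so they are assumptions. The difference of 51.48 and SD of 97 are assumed to hold within the microalbuminuria stage. The last column also assumes the same standardised effect for urinary protein. For share s, power = Φ(0.5305 × √(56s / 1.5) - z), with z = 1.960 at 0.05 and 2.241 at 0.025. The last column multiplies the two stages' power at 0.05.

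| Microalbuminuria share | UAER power, 0.05 | UAER power, 0.025 | Both required |
|---|---|---|---|
| 30% | 43% | 32% | 33% |
| 40% | 54% | 42% | 38% |
| 50% | 63% | 52% | 40% |
| 60% | 71% | 61% | 38% |
| 70% | 77% | 68% | 33% |

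For an either-rule at a 50% share with equal effects, power is 1 - (1 - 0.630)² = 86% at 0.05 each, and 1 - (1 - 0.520)² = 77% at 0.025 each.

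**Figure 1 read literally.** If every patient were tested on both measures, the tests would be correlated. The either-rule error would be 9.5%, 9.1%, 8.3% or 7.0% for assumed correlations of 0.3, 0.5, 0.7 or 0.9.

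**The case against.** **The analysis plan may settle it.** The success rule and the division of alpha often sit in a statistical analysis plan, and one may exist that is not shown. Their absence alone is not a defect, and that stands. But the primary outcomes, the patients they apply to, and the alpha and power that justify the sample size are fixed in the protocol, and there they do not match. An analysis plan that tests the stages separately cannot make the stated sizing fit.

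**No section says that either result suffices.** A reader might infer that the false-positive rate is nearly double the stated 5%. The document does not support that as a fact. The outcome sentence names measurements rather than tests and joins them with a conjunction. It is equally consistent with requiring both or with one stage-stratified test, and under those the error is at most 5%. The 9.75% is conditional.

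**Figure 1 may be shorthand.** A reader might take it to name a different primary set, or count both measures in both stages as four independent primary tests. Neither is supported. It lists the same two measures and leaves out the stage. No section specifies four tests, and independence between two measures of urinary protein loss in the same patients is not credible. Read literally, with both measures tested in everyone, it gives an either-rule error below 9.75%. It needs aligning and does not add to the error rate.

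**The power figures rest on assumptions.** This is fair. The SD is back-solved, the stage shares are unknown, and the spread of UAER within one stage may differ. With half the patients and the same difference, 90% would need an SD of about 97 × √0.5 = 69, and nothing in the protocol indicates that. For urinary protein no effect is given at all. The both-required power still cannot exceed UAER's power in its own stage, whatever the protein effect.

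**Separate patients are assumed.** The stage definitions lie in a cited guideline. The entry criterion, "and/or 24-hour urinary protein level 0.5~2.0 g", does not itself assign a patient to a stage.

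**Conclusion.** The point holds as a mismatch within the protocol. The stage-specific primary outcomes and the single UAER-based sample size do not describe the same comparison, and the protocol leaves open what counts as success.

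On the sizing shown, and with equal standardised effects, no rule that tests the stages separately delivers both 5% error and 90% power. At a 50:50 split:
- either at 0.05 gives 9.75% error and 86% power;
- either at 0.025 gives 4.9% error and 77% power;
- both required keeps error at or below 5% with about 40% power.

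The error figures are arithmetic, given disjoint stages. The power figures depend on the back-solved effect of about 0.53 and on assumed stage shares, so they indicate size and are not estimates for this trial. One test over all patients could keep 5% and 90%, if its standardised effect is about 0.53, but the Primary outcomes section does not describe one. Because this governs the main efficacy claim, it should be settled before unblinding.

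**What to change.** Make the Sample size section, Figure 1 and the Primary outcomes section agree. Before unblinding, name one primary test at two-sided 0.05 in all patients. It would use each patient's stage-specific measure on a common relative scale, for example the log ratio of week 24 to baseline, stratified by stage and adjusted for baseline. State how each patient's stage is assigned at baseline, and restate the planning effect and SD on the scale that will be tested.

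If two primary outcomes are kept, state the success rule. If either suffices, use Hochberg or 0.025 each. In all cases restate the power for each stage. As a guide, 90% power for UAER in its own stage at 0.025 would need 67 controls and 134 on TSF, 201 evaluable in that stage alone, with the back-solved effect.

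The single test needs only wording in three places and a few lines of analysis code. It needs no extra patients or data, since Table 1 already collects both measures at baseline and week 24. The small downside is that it yields one overall effect, so the stage-specific results become supportive.

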**Secondary outcomes**

The following domains are recognized as the secondary outcome measurements, including: renal function, regarding serum creatinine (Scr), blood urinary nitrogen（BUN）and eGFR measured by Cockcroft-Grault equation with a 0.85 correction factor for women; blood lipid, containing total cholesterol (TC), triglyceride (TG), high density lipoprotein-cholesterol (HDL-C)and low density lipoprotein-cholesterol (LDL-C); glycemic management (assessment by HbA1c); the improvement of TCM symptoms (evaluation by TCM symptomatology scores; the improvement of quality of life (QOL) (assessment by WHO QOL-BREF and Diabetic Scall of Quality of Life of Chinese).

**Safety assessment**

The results of blood, urine routine tests, electrocardiogram (ECG), ALT and AST tests will be the comprehensive reflection of safety assessment.

**Adverse events**

Adverse events (AE) refer to adverse medical events occur after treatment with a drug, which do not necessarily have a causal relationship with the treatment. Serious adverse events (SAE) include death, hospitalization or prolonged length of hospitalization, disability and congenital malformations. We have established the adverse event monitoring system and defined the three-grade criteria of adverse events: the first level as it could be endured or only mild discomfort with no affection of daily life; the second level as it causes discomfort and affects daily life; the third level as it causes handicap to self-care ability.

**Possible adverse events due to TSF:** TSF contains the herbal medicine rhubarb, which may lead to the following adverse events to participants: 1) Diarrhea and secondary constipation: Loose stools and diarrhea are the most common adverse reactions of rhubarb. Severe cases may have symptoms of dehydration, such as sunken eyes, dry lips and fatigue. Tannic acid in rhubarb has anti-diarrhea action. Taking rhubarb for a long time can cause stress reaction reduction of intestinal nerve cell, leading to rhubarb dependent constipation. 2) Melanosis coli: Herbal medicine with strong cathartic actions usually contains anthraquinone derivatives, which may cause colon melanosis coli. Diagnosis of melanosis coli is mainly based on microscopic examination and biopsy specimens. Taking rhubarb for a long-term or with a high dosage can increase the secretion of intestinal mucus glands, make intestinal epithelial cells produce more histocompatibility complex, and increase macrophage activity and chemotaxis. Then the macrophage phagocytosis is strengthened, causing colon melanosis coli. 3) Other adverse events: A few cases reported that application of rhubarb might cause elevated ALT and serum creatinine, which were mainly due to excessive intake without instruction of a physician.

**Possible adverse events due to ACEIs/ARBs:** The main side effects of ACEIs and ARBs are dry cough, rise of serum potassium and rise of serum creatinine.

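### The adverse-event severity scale is purely functional, so a symptomless laboratory adverse event of any size can only be level 1 or ungraded

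*Protocol*

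**What the plan says.** The Adverse events section of the protocol sets three severity levels:

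- Level 1: "the first level as it could be endured or only mild discomfort with no affection of daily life".
- Level 2: "the second level as it causes discomfort and affects daily life".
- Level 3: "the third level as it causes handicap to self-care ability".

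Under possible adverse events due to TSF, the same section states that "application of rhubarb might cause elevated ALT and serum creatinine", and adds that the reported cases were "mainly due to excessive intake without instruction of a physician". For the ACEI or ARB that every participant receives, it names "dry cough, rise of serum potassium and rise of serum creatinine".

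The Safety assessment section says: "The results of blood, urine routine tests, electrocardiogram (ECG), ALT and AST tests will be the comprehensive reflection of safety assessment". Serum creatinine is a secondary outcome. Table 1 schedules ALT, AST and creatinine at weeks -2, 0, 12 and 24.

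**The concern.** The protocol counts laboratory changes among its adverse events and builds its safety assessment largely on laboratory tests. Yet the only severity rule it gives asks how the patient feels and functions. Liver enzyme and creatinine rises often cause no symptoms, and the scale has no means of ranking those that do not.

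What is at stake is the meaning of a severity summary. If adverse events are reported by level, symptomless liver and kidney events would either sit in the lowest level or be absent from the summary. A sentence saying that the laboratory adverse events were mild could then reflect the scale and not the data. Investigators at six hospitals would also have no common rule for such an event: one site might record level 1 and another might leave the grade blank.

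**Working it through.** There is no figure to reproduce. The check is to apply each level to a symptomless laboratory event, and then to look for any other rule in the protocol that would grade it.

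**Step 1. Apply the scale.** Take a rise in ALT or creatinine that the patient does not notice.

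| Level | What it requires | Met by a symptomless rise? |
| --- | --- | --- |
| 3 | Loss of the ability to care for oneself | No |
| 2 | Discomfort together with an effect on daily life | No, neither part is met |
| 1 | Endurable, or mild discomfort with daily life unaffected | Only by reading a symptomless event as endurable |

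Two outcomes remain: level 1, or no grade. The size of the rise enters none of the three definitions. As an illustration, an ALT just above 2 times the upper limit of normal and one at 10 times the limit are treated alike.

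**Step 2. Look for a rule elsewhere.**

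- The definition of a serious adverse event, in the same section, concerns outcome: death, hospitalization or its prolongation, disability, congenital malformation. It is a matter of seriousness and has no laboratory criterion.
- The five grades in Quality control classify the relation to the drug, not severity.
- The ALT/AST limit of 2 times the upper limit, in Inclusion and exclusion criteria, is an entry criterion. It is not used for events on treatment.
- Safety assessment names the tests and gives no threshold.

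Nothing else in the protocol supplies a laboratory severity criterion.

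**Step 3. Establish what is not affected.**

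- ALT and AST results enter the safety assessment directly, whatever grade an event receives.
- Creatinine is collected and analysed as a secondary outcome.
- A laboratory event that leads to hospitalization is serious, whatever its level.

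Large changes therefore stay visible in the data. What fails is the severity grade.

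**Step 4. Is this a matter for the SAP?** How abnormal values are tabulated commonly is, and no fault is found there. The severity scale is different: the protocol fixes it, and investigators apply it as events occur. A later analysis plan can tabulate the grades but does not change how the sites assign them.

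**The case against.** The strongest defence is that the protocol reads laboratory safety from the test results and not from the severity level. It plans no severity table and nowhere says that the safety conclusion depends on the three levels. Grading by functional impact is a recognised mild, moderate and severe approach, and it suits diarrhea, which the protocol calls the most common reaction to rhubarb. Quality control also requires the type, timing, manifestation, treatment and prognosis of each adverse effect, so the level is one item among several. All of this stands, and it limits the point to severity grading.

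A reader might infer more than the protocol supports:

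- **That the safety conclusion for TSF rests on a severity table.** The protocol does not say so, and Safety assessment points to the results themselves.
- **That every such event must be placed at level 1.** The protocol does not say how symptomless laboratory events are graded. Level 1 is one reading and no grade is the other.
- **That all ALT, AST and ECG results in the roughly 128 patients allocated to TSF (192 × 2/3 = 128) are affected.** The scale grades adverse events, not test results.
- **That the protocol expects raised ALT and creatinine under TSF.** It lists them as possible, from a few reported cases, mostly with excessive unsupervised intake.
- **That potassium belongs to the same point.** It is named as a side effect of ACEI or ARB, but no row of Table 1 names serum potassium. The argument that the values are already collected cannot be made for it.

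The defence does not remove the mismatch inside one section, which names laboratory adverse events and then sets a scale that cannot rank them. Leaving such events ungraded would not be a repair.

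**Conclusion.** The point holds within narrow limits. As worded, the severity scale gives a symptomless laboratory adverse event level 1 or no grade, however large the change. Any summary of adverse events by severity would be uninformative for that class. Detection, the laboratory results and the reporting of serious events are not impaired.

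The size cannot be put in numbers: the protocol gives no rate of laboratory adverse events, and none can be derived from it. By wording alone, the loss of information is complete for symptomless laboratory events and nil for events that are adequately described by symptoms.

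This rests on two assumptions: that the affected events are truly symptomless, and that no other trial document, such as site instructions, supplies a laboratory grading rule. The change is worth making because it is cheap and the rule is applied at the sites. It bears on neither the primary outcome, the sample size nor the randomization.

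**What to change.** In the Adverse events section:

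1. Keep the three functional levels for symptoms.
2. Grade laboratory adverse events in ALT, AST and creatinine on a named standard numeric toxicity scale, using multiples of the upper limit of normal for ALT and AST and multiples of baseline for creatinine. State how its grades map to the three levels.
3. Where an event has both a functional and a numeric grade, record the higher.
4. Report laboratory adverse events by numeric grade and treatment arm.

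The cost is about one paragraph in the protocol and a matching line in the CRF guidance. No visit or test is added, because ALT, AST and creatinine are already measured at weeks 0, 12 and 24. The change concerns classification and reporting only, and alters no dose or rule of clinical management. The downside is that some events will carry a higher, less favourable grade.
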